### Data management

Trained research associates will perform data checks for accuracy and completeness. Using an electronic case report form, the data will be entered into the database. The collected data will be kept in the central data archive of the data center, which has a built-in security feature preventing unauthorized access to confidential participant information.

### Data analysis

While intention-to-treat analysis will be primarily performed for all patients enrolled in the study, per-protocol analysis will also be performed for patients who follow the study protocol without violation. Intra-individual comparison will be made between B-mode US and contrast-enhanced US in terms of the detection rate of early-stage HCC, the false referral rate, and the detection rate of any stage HCC using McNemar’s test in a per-patient manner.

Subgroup analyses will be performed for each endpoint according to a patient’s age, gender, body mass index, cirrhosis etiology, history of anti-viral treatment, Child-Pugh score, Albumin-Bilirubin (ALBI) grade [28], and alpha-fetoprotein (AFP). We will use logistic regression models with a generalized linear mixed model (GLMM) including random intercept for the patients if the study results show considerable variation across the participating institutions. *P* values less than 0.05 are considered statistically significant. All statistical analyses will be performed using commercially available software (SAS Ver. 9.2; SAS Institute, Cary, NC, USA).

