### Primary endpoints

The primary study endpoints are a detection rate of early-stage HCC and a false referral rate. The detection rate of early-stage HCC is defined as the proportion of patients having both positive US results and confirmed as having early-stage HCCs on reference standard procedures out of all patients enrolled in the study. The early-stage HCC is defined as a single HCC<5cm or up to three HCCs, each of which is less than 3 cm based on the Barcelona Clinic Liver Cancer staging system (BCLC stage 0 or A) [25]. The false referral rate is defined as the proportion of patients having positive US results but confirmed as not having HCC on reference standard procedures out of all patients enrolled in the study.

The likelihood of HCC = grade 3 will be regarded as test positive both for B-mode US and contrast-enhanced US. If a patient has two or more lesions, the lesion assigned the greatest likelihood of HCC will be regarded as the representative lesion of that patient. As patients who have positive results either on B-mode US or on contrast-enhanced US subsequently undergo reference standard procedures, the true-positives and false referrals are to be determined by comparing the case report forms of each US method with the reference standards. For example, if a patient has a lesion of which the likelihood of HCC is grade 3 on B-mode US but is grade 2 on contrast-enhanced US, and if the patient is finally confirmed as not having HCC on reference standard procedures, it will be counted as a false referral of B-mode US but not of contrast-enhanced US.

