### Sample size

For sample size calculation, we assumed a 5% prevalence of HCC in our target population, a 3.15% detection rate of early-stage HCC on B-mode US (63% of sensitivity)[27],and a4.75% detection rate of early-stage HCC on contrast-enhanced US (95% of sensitivity) [8]. We also assumed a 1.7% discordant rate which included0.05% of the proportion of patients in whom a lesion is detected on B-mode US but not on contrast-enhanced US. With these assumptions, 523patients are needed to obtain 80% statistical power for the McNemar’s test with an α equal to 0.05.

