### Study endpoints

The accuracy of a diagnostic test can ideally be evaluated with a definitive diagnosis, usually in terms of sensitivity and specificity. However, studies investigating the efficacy of US in surveillance settings have frequently been limited by verification bias [27]. This is because the definitive diagnostic procedure is used on patients who have positive results, while those who have negative results are not confirmed as true or false negatives, which indicates that neither sensitivity nor specificity is identifiable [29]. A detection rate and a false referral rate are two important reciprocal measures which do not require definitive diagnoses from all study patients and allow a comparison of the relative performance of two screening tests [29, 30]. While we expect improvement of the detection rate of early-stage HCC by adding contrast-enhanced US to conventional B-mode US, the improvement can be truly valuable only if the false referral rate is decreased or at least remains stable.

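### McNemar's test can show that the co-primary false referral rate has fallen, but not that it has stayed stable, which is the other outcome the article says would make a detection gain valuable

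*Protocol article*

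**What the plan says.** The Primary endpoints section names two primary endpoints: "The primary study endpoints are a detection rate of early-stage HCC and a false referral rate". A false referral is a positive ultrasound result in a patient whom the reference standard shows not to have HCC, counted over all enrolled patients.

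The Data analysis section gives this endpoint the same test as the detection rates: it states that "Intra-individual comparison will be made between B-mode US and contrast-enhanced US in terms of the detection rate of early-stage HCC, the false referral rate" and any-stage detection, by McNemar's test on a per-patient basis. The threshold is that P "values less than 0.05 are considered statistically significant".

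The Discussion (Study endpoints) says what the false referral rate has to show: a detection "improvement can be truly valuable only if the false referral rate is decreased or at least remains stable".

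The Sample size section uses only early-stage detection rates and their discordance, and concludes that "523patients are needed to obtain 80% statistical power for the McNemar’s test with an α equal to 0.05". It assumes nothing about false referrals.

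**The concern.** The Discussion accepts two outcomes for false referrals: a fall, or no material rise. The stated analysis can establish only the first. If the test is not significant, the data may fit equal rates, or they may fit a rise that the trial was too imprecise to detect. McNemar's test does not separate these cases, and the less precise the comparison, the more easily a rise passes as no difference.

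The trial's main message is at stake. The article aims to show whether contrast-enhanced ultrasound finds more early HCC without adding unnecessary examinations. Under the stated test, the second half of that message could rest only on a non-significant P value, unless the rate actually falls significantly.

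**Working it through.** **Step 1. Reproduce the plan's own figure.** Inputs from the Sample size section:
- detection 3.15% on B-mode and 4.75% on contrast-enhanced ultrasound, a difference of 1.60 points;
- total discordance 1.7%, of which 0.05% is B-mode only, leaving 1.65% contrast-enhanced only.

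Exact two-sided McNemar test: the number of discordant pairs m is Binomial(n, 0.017). Given m, the number in favour of contrast-enhanced ultrasound is Binomial(m, 0.0165/0.017). Summing the rejection probability over m gives power of 79.96% at n = 522 and 80.08% at n = 523. So 523 is reproduced and is sound for early-stage detection.

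**Step 2. Chance that a real rise in false referrals is missed.** The documents give neither a false referral rate nor its discordance, so total discordance is assumed to be 2% to 8%. For illustration the true rise is set at 1.6 points, the same size as the planned detection gain (4.75 − 3.15). The discordant cells are then (discordance ± 1.6)/2; at 4%, for example, they are 2.8% and 1.2%. The test is the exact two-sided McNemar test at 0.05 with n = 523.

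| Assumed discordance | Power to detect the rise | Trials with a non-significant result |
|---|---|---|
| 2% | 69% | 31% |
| 3% | 48% | 52% |
| 4% | 37% | 63% |
| 6% | 26% | 74% |
| 8% | 21% | 79% |

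**Step 3. Precision of the paired difference.** Approximate half-width of the 95% interval = 1.96 × √(discordance/523):
- 2%: 1.96 × √(0.02/523) = 1.2 points
- 3%: 1.5 points
- 4%: 1.7 points
- 6%: 2.1 points
- 8%: 1.96 × √(0.08/523) = 2.4 points

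**Step 4. What a margin-based criterion could deliver with 523 patients.** If the true rates are equal, the probability that the upper 95% limit lies below a margin M is about Φ(M/√(discordance/523) − 1.96). At 4% discordance the standard error is √(0.04/523) = 0.875 points. So M = 2.5 gives Φ(2.86 − 1.96) = 82%, and M = 1.6 gives Φ(1.83 − 1.96) = 45%.

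| Assumed discordance | Power, 2.5-point margin | Power, 1.6-point margin |
|---|---|---|
| 4% | 82% | 45% |
| 6% | 65% | 32% |
| 8% | 52% | 25% |

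Both margins are illustrations; the documents state none.

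**The case against.** **The stability remark is Discussion prose, not a decision rule.** This is correct. A reader might infer that the plan makes stable false referrals a formal condition of success, but the Data analysis section lists separate comparisons and states no success criterion. The remark is still the authors' own standard for interpreting a primary endpoint, and the stated test cannot meet half of it.

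**Nothing says that P≥0.05 will be read as stability.** That is also true. The point is only that the article offers no other route to such a claim.

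**A margin and an interval method may stand in an analysis plan that is not shown.** Their absence alone would not be a finding. But the article does not leave this analysis open: it names the test and the threshold for this endpoint, and says elsewhere what the endpoint has to show. These two statements do not match.

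**A reader might infer that significance on either primary endpoint would count as success, with a type I error of 1 − 0.95² = 9.75%.** The documents do not support this. The Discussion points the other way, since it ties the value of a detection gain to the false referral rate. The figure also counts results that favour B-mode. For favourable false claims alone, two independent tests give 1 − 0.975² = 4.9%.

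**A reader might take 1.6 points as the plan's own margin.** It is not. The Sample size section uses it only as the expected detection gain, and no section links it to false referrals.

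**The size rests on assumed discordance.** This stands. At 2%, the half-width is below 1.6 points and the test detects the rise in 69% of trials. The range is therefore shown in full, including its favourable end.

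**Conclusion.** The concern holds as a mismatch between the stated test and the stated aim for a primary endpoint. McNemar's test can support a claim that false referrals fell, but not a claim that they remained stable. The sample size of 523 is correct for early-stage detection, and its 80% power does not extend to false referrals.

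With assumed discordance of 2% to 8%, a true 1.6-point rise would be non-significant in about 31% to 79% of trials. These figures depend on the discordance and on the size of rise chosen, neither of which comes from the documents. That an equality test cannot establish stability depends on neither.

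**What to change.** In Data analysis:
- Report the paired difference in false referral rate (contrast-enhanced minus B-mode) with a two-sided 95% confidence interval, for example the Tango score interval.
- Claim stability only if the upper limit lies below a margin that the investigators choose and justify before the comparison is run.
- Claim a decrease only if the upper limit lies below zero.
- State that stability will not be inferred from P≥0.05.
- Describe a detection gain as free of added unnecessary work-up only if both the detection test and this criterion are met.

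In Sample size, state that the 80% power refers to early-stage detection only.

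The cost is wording. No patients or data are added, and the Design section reports that follow-up for the primary endpoint was still ongoing after the last enrolment in August 2016, so the rule could be set before the comparison. The price is a possibly weaker conclusion: 523 patients may not settle stability even if the rates are truly equal, and the report would then have to say that the question remains open.

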## Discussion

### Study design

We designed SCAN as an intra-individual comparison study rather than a randomized controlled trial (RCT). Due to the lack of previous researcher grading contrast-enhanced US in surveillance, it was impossible to set the appropriate effect size for an RCT. The lack of baseline data also raised a concern regarding the equipoise that could justify the randomization. Although we could not use the design of an RCT, intra-individual comparison has obvious advantages as it would allow for an excellent comparability between a pair of results and would also increase the statistical power for a given number of study patients. Unlike typical therapeutic or interventional trials, the diagnostic examinations investigated in diagnostic trials can be repeatedly applied to the same patient without affecting the disease status. We expect that the results of SCAN will offer not only the efficacy of contrast-enhanced US but also relevant baseline data for future studies on US surveillance.

### Study endpoints

The accuracy of a diagnostic test can ideally be evaluated with a definitive diagnosis, usually in terms of sensitivity and specificity. However, studies investigating the efficacy of US in surveillance settings have frequently been limited by verification bias [27]. This is because the definitive diagnostic procedure is used on patients who have positive results, while those who have negative results are not confirmed as true or false negatives, which indicates that neither sensitivity nor specificity is identifiable [29]. A detection rate and a false referral rate are two important reciprocal measures which do not require definitive diagnoses from all study patients and allow a comparison of the relative performance of two screening tests [29, 30]. While we expect improvement of the detection rate of early-stage HCC by adding contrast-enhanced US to conventional B-mode US, the improvement can be truly valuable only if the false referral rate is decreased or at least remains stable.

### Composite reference standards

We set composite reference standards in SCAN, which uses either histopathology or radiology as the final diagnosis of HCC. Various treatments, such as surgery, radiofrequency ablation, percutaneous ethanol injection, and combined therapy of radiofrequency ablation and trans-arterial chemoembolization, are currently available for early-stage HCCs [1, 2, 31]. This makes the investigation of the efficacy of a diagnostic test for HCC more complex as histopathology, which has traditionally been used as the reference standard for imaging diagnosis, is not available in most patients. Furthermore, the very high specificity of the typical radiological features of HCC in an at-risk population rendered the imaging diagnosis a substitute for histopathology, and the recently updated American Association for the Study of Liver Diseases (AASLD) guidelines have even proposed that one imaging technique (either CT or MRI) showing the typical radiological features suffices for diagnosing HCC [2]. It is now regarded as unethical to perform a biopsy on a patient with HCC, in whom the biopsy is unnecessary for clinical purposes. If we use only histopathology as the reference standard, it should result in a significant bias as then only HCCs showing atypical radiological features will be included as true HCCs.

### Imaging criteria for the likelihood of HCC

As the imaging criteria for the likelihood of HCC are not protocolled in SCAN, the diagnosis will be left to the discretion of the radiologists who conduct and interpret the US. In previous research studies evaluating the efficacy of US in the surveillance setting, the criteria defining which lesion should trigger further investigation were usually absent or, if any, they differed from the other criteria [32–43]. Considering the subjectivity of US interpretation and the diverse sonographic features of HCC [44], the current guidelines often suggest that any new lesion detected on US, regardless of its echogenic pattern, should be further evaluated by CT or MRI. However, there is still a discrepancy between the guidelines regarding the use of the size criterion. While AASLD and The European Association for the Study of the Liver (EASL)guidelines suggest a 1-cm criterion [1, 2], guidelines from the Asian-Pacific region do not have such a criterion in the diagnostic algorithms [3, 45, 46]. Furthermore, the clinical significance of a lesion smaller than 1 cm and showing a defect on Kupffer-phase US has not yet been established. Therefore, we have decided not to list specific imaging criteria for the likelihood of HCC which do not reflect current variations in clinical practice.

SCAN is the first study to investigate the efficacy of contrast-enhanced US in surveillance using two reciprocal endpoints specialized for evaluation of a surveillance test. SCAN will provide evidence regarding whether patients can truly benefit from contrast-enhanced US in terms of the detection of early stage HCC while avoiding additional unnecessary examinations.

## Abbreviations

AFP: Alpha-fetoprotein
ALBI: Albumin-Bilirubin
BCLC: Barcelona Clinic Liver Cancer staging system
CTCAE: Common Terminology Criteria for Adverse Events
EASL: The European Association for the Study of the Liver
GLMM: Generalized linear mixed model
HCC: Hepatocellular carcinoma
LI-RADS: Liver Imaging Reporting and Data System
PACS: Picture archiving and communications system
RCT: Randomized controlled trial
SAEs: Serious adverse events
US: Ultrasonography
